# Church-based problem-solving therapy for adolescent girls and young women with a history of gender-based violence in Zambia: study protocol for a hybrid type 1 randomized controlled trial

**DOI:** 10.1186/s13063-026-09625-3

**Published:** 2026-04-10

**Keywords:** Gender-based violence (GBV), Adolescent girls and young women (AGYW), Problem-solving therapy (PST), Church-based intervention, Hybrid type 1 implementation-effectiveness trial, HIV prevention and treatment, Mental health, Zambia, Lay counselors, Implementation science

## Abstract

**Background:**

Adolescent girls and young women (AGYW) in sub-Saharan Africa face a disproportionate burden of gender-based violence (GBV), HIV risk, and mental health challenges. Despite the demonstrated effectiveness of psychological interventions such as problem-solving therapy (PST), there is limited evidence on culturally adapted models for GBV-exposed AGYW that concurrently address HIV and mental health, particularly in settings with constrained mental health infrastructure.

**Objective:**

This study outlines the protocol for a randomized controlled trial evaluating *Mpata Yathu*, a church-based adaptation of the Friendship Bench intervention, which delivers lay counselor-led PST to AGYW with a history of GBV in Lusaka, Zambia.

**Methods:**

A hybrid implementation-effectiveness type 1 randomized controlled trial (intervention and waitlist control arms) will be conducted among 90 AGYW, aged 15 to 24, per arm with moderate depressive symptoms, lifetime GBV exposure, and HIV risk or diagnosis. The intervention comprises six individual PST sessions delivered over 3 months in church spaces. Implementation outcomes (feasibility, acceptability, fidelity), common mental disorder (CMD) symptoms (primary outcome), and exploratory outcomes (depression, anxiety, PTSD, HIV engagement, GBV attitudes, childhood adversity, coping self-efficacy) will be assessed at baseline, 3, and 6 months. The trial is powered to detect changes in CMD symptoms only. Mixed-methods data will inform feasibility, intervention refinement, and hypotheses regarding mental health as a mediator of HIV outcomes. Process evaluations will use the Consolidated Framework for Implementation Research (CFIR).

**Conclusions:**

This trial will assess the potential of church-based PST to address the intersecting burdens of GBV, HIV, and mental health among AGYW in Zambia. Findings will offer insights into leveraging trusted community institutions (e.g., church and religious settings) for mental health and HIV care delivery in low-resource settings.

**Trial registration:**

ClinicalTrials.gov NCT07132905. Prospectively registered on August 13, 2025. clinicaltrials.gov/study/NCT07132905.

**Supplementary Information:**

The online version contains supplementary material available at 10.1186/s13063-026-09625-3.

## Background

Young Zambian women face a dual burden of gender-based violence (GBV) and HIV, which is further compounded by mental health challenges. GBV refers to violence that is explicitly or implicitly directed at a person because of their gender and disproportionately affects women and girls [1]. GBV is inextricably linked to heightened HIV risk, primarily due to structural and social factors such as unequal gender power dynamics and patriarchal gender norms that restrict women’s ability to negotiate safe and consensual sex [2–4]. Adolescent girls and young women (AGYW), classified as women aged 15 to 24, face increased vulnerabilities. In Zambia, as in much of sub-Saharan Africa, studies consistently show that intimate partner violence (IPV), a form of GBV occurring within intimate relationships [5–7], is strongly associated with HIV seropositivity in this demographic. For instance, a pooled analysis across 30 sub-Saharan African countries, including Zambia, found that women who experienced past-year physical or sexual IPV were over three times more likely to acquire a recent HIV infection and were significantly less likely to achieve viral suppression [7]. Furthermore, physical violence, psychological abuse, or forced sex is associated with higher odds of viremia among young Zambians living with HIV [8]. GBV-exposed women are also at risk for mental health disorders including depression, anxiety, PTSD and substance misuse [5, 9–15]. GBV and mental health disorders also undermine HIV prevention and treatment engagement by decreasing antiretroviral therapy (ART) adherence, clinic attendance, and pre-exposure prophylaxis (PrEP) use [2, 8, 16–18].

Although the integration of mental health treatments within HIV interventions can lead to improvements in HIV and mental health outcomes, there is insufficient evidence of this impact among young women with a history of GBV, particularly in settings with limited human resources for health services like Zambia [19]. Mental health treatment in Zambia is constrained by limited numbers of mental health specialists such as psychiatrists, psychologists, nurses, or clinical social workers. According to the World Health Organization, Zambia has a critical shortage of mental health specialists, with approximately 0.06 psychiatrists and 1.43 mental health nurses per 100,000 people [20]. Instead, task-shifting approaches that utilize paraprofessional mental health support persons, such as psychosocial counselors, peer supporters and community health workers, have emerged as promising, cost-effective strategies for bridging the treatment gaps in behavioral and mental health care [21, 22]. This phenomenon is not unique to Zambia. Paraprofessional mental health support has successfully been used to address the mental health provider deficit in several contexts throughout sub-Saharan Africa [21, 23, 24].

Local Zambians affirm the need to leverage the sociocultural influence of the church to offer counseling and other rehabilitative services to GBV survivors [25]. Church leaders are widely trusted to provide counseling and support for GBV survivors [25]. They are often the first lines of contact in GBV-related situations in families [26]. A range of GBV-related support practices were adopted by Pentecostal churches in Lusaka to address GBV, including sponsoring couples’ meetings and home visitations, as well as providing moral, spiritual, and financial support [25]. However, both clergy and lay members emphasized the untapped potential of churches to play a more active role in offering counseling services, particularly if church leaders receive appropriate training [25, 26]. Church leaders particularly expressed interest in being trained in counseling to support women who have experienced violence [25]. Given the moral authority of religious leaders and the influence of church teachings on social norms, including norms related to GBV and HIV risk behaviors [27], the church represents a promising platform for integrated GBV and HIV interventions. Despite this potential, there remains a striking lack of rigorous evaluations assessing the effectiveness of church-led GBV-HIV programs, and evaluations of implemented GBV-HIV interventions by the church remain scarce [28]. This presents a missed opportunity to strengthen and scale up church-based GBV support for young women, who are often overlooked in existing church-based responses that focus primarily on married couples [25].

This study is a hybrid type 1 (HT1) [29] randomized controlled trial designed to evaluate the effectiveness of a church-based problem-solving therapy intervention, called *Mpata Yathu* (meaning “Our Space” in Chinyanja), for adolescent girls and young women in Zambia, while concurrently assessing implementation outcomes such as fidelity, acceptability, and feasibility. *Mpata Yathu* is an adaptation of the Friendship Bench, an evidence-based, lay-delivered problem-solving therapy (PST) intervention originally developed in Zimbabwe [30]. In this adapted version, *Mpata Yathu* is designed specifically for AGYW in Lusaka, Zambia who have experienced GBV and are either living with or at risk of acquiring HIV. The intervention will be delivered in church settings, leveraging the church’s trusted position and widespread community influence to increase accessibility, acceptability, and relevance.

This protocol outlines the objectives of the *Mpata Yathu* HT1 RCT which aim to:*Aim 1:* Assess the effect of the intervention on common mental health disorder (CMD) symptoms, the primary outcome for which the study is statistically powered.*Aim 2:* Evaluate the implementation outcomes of the Mpata Yathu intervention, specifically its feasibility, acceptability, and fidelity, as delivered by lay counselors to AGYW with a history of GBV experiences.*Aim 3:* Explore potential effects of the *Mpata Yathu* intervention on:oAdditional mental health outcomes (depression, anxiety, PTSD);oHIV prevention and treatment engagement outcomes (based on participant HIV status);oGBV-related attitudes and experiences, and psychosocial variables (e.g., adverse childhood experiences and coping self-efficacy).oWhether changes in mental health symptoms mediate or moderate the intervention’s effects on HIV-related outcomes.

### Description of the intervention

*Mpata Yathu* is a church-based, lay counselor-delivered psychological intervention that we will evaluate in Lusaka, Zambia. The intervention is an adaptation of the Friendship Bench model. Friendship Bench, a globally recognized mental health model and originating from Zimbabwe, is a culturally responsive intervention comprising weekly PST sessions that are delivered on a bench by lay counselors who are older adult women, known as grandmothers [30]. Friendship Bench significantly reduced mean depression scores, as measured by the Patient Health Questionnaire-9 (PHQ-9) [31], by 6.36 points after a 6-month follow-up period among Zimbabwean adults (86% women, 42% HIV seropositive) [24]. The 6.36-point reduction in PHQ-9 scores is clinically meaningful because it exceeds the commonly accepted threshold for significant symptom improvement [32]. However, a cluster-randomized trial in rural Zimbabwe found that the Friendship Bench intervention significantly reduced symptoms of common mental disorders but had no significant impact on ART adherence or viral suppression among people living with HIV [33]. This suggests that while Friendship Bench is effective for mental health, additional integrated HIV care strategies (e.g., HIV linkages and follow-up) may need to be adapted to address HIV prevention and treatment outcomes among GBV survivors.

*Mpata Yathu*has been specifically tailored for AGYW aged 15 to 24 who have experienced GBV and are living with or at risk for HIV. Using principles of Community-Partnered Participatory Research (CPPR), we relied on community partner feedback to guide the adaptation process [34, 35]. In CPPR, community partners are individuals and organizations that represent and serve the community, bringing local knowledge, lived experience, and leadership to shape and guide all phases of the research [34]. The process of developing the adaptation is described elsewhere. This adaptation maintains the core principles of the original Friendship Bench intervention—namely, structured PST that supports participants in identifying and addressing personal problems—but introduces several critical modifications. These include training lay counselors on how to navigate GBV-related conversations and referrals among their clients, integrating trauma-informed and survivor-centered approaches into counseling delivery and practice (i.e., allowing clients to choose their counselor), and situating the delivery within church spaces to leverage the social authority and reach of religious institutions in Zambia. Church-based delivery is intended to reduce barriers to access by situating the intervention within trusted and familiar community environments, while also capitalizing on the role of churches as influential actors in shaping norms related to gender, mental health, and HIV.

Unlike the original model which deploys “grandmothers” to deliver the intervention, *Mpata Yathu* will be implemented by lay counselors with diverse backgrounds and age ranges (e.g., young adults, middle-aged, pastors, schoolteachers, students, peer navigators, etc.) and the clients will choose their counselor in the order of their preference. Allowing choice by the clients was intended as part of our trauma-informed, survivor-centered approach. Trained lay counselors will deliver the intervention within church settings following an intensive training program that includes PST techniques, ethical protocols, and guidance on supporting GBV survivors. Each participant will be offered six weekly sessions lasting approximately 45–60 min. In addition to PST delivery, the intervention includes structured referral pathways to mental health/psychiatric support, HIV services, and GBV response mechanisms, ensuring participants receive appropriate and timely care beyond the sessions themselves.

In a feasibility trial evaluating PST for pregnant women experiencing depressive symptoms and IPV in rural Ethiopia, participants were randomized into one of three arms: PST adapted for IPV (PST-IPV), standard PST, or enhanced usual care [36]. While the study found high acceptability and feasibility across arms, the adapted PST-IPV arm did not lead to more IPV-related content being discussed in sessions. These findings informed our decision to initially implement the standard PST model without IPV-specific modifications. However, we will monitor implementation closely and use process evaluation findings to determine whether future adaptations are necessary to better support GBV-related coping and problem-solving.

Although problem-solving therapy has demonstrated promise in improving mental health outcomes, particularly depression, among diverse populations, there remains limited evidence on its specific effectiveness for women who have experienced GBV. In a systematic review and meta-analysis, psychological interventions, including PST, were effective at reducing anxiety among women experiencing IPV in low- and middle-income countries (LMICs), even when the interventions were not specifically tailored to address IPV [37]. Another systematic review and meta-analysis reported only modest mental health benefits from psychosocial interventions with no impact on IPV recurrence [38]. Both reviews underscore the need for more rigorous, targeted research on the effectiveness and adaptation of PST for GBV survivors.

### Theoretical/conceptual model

Conroy et al. [18] conducted a longitudinal study of over 1700 women living with HIV in the USA, and found that GBV is significantly associated with a higher odds of suboptimal medication adherence and missed clinical appointments [18]. The authors also found that mental health mediates the relationship between GBV and HIV treatment engagement. Depression, general anxiety disorder, and PTSD symptoms were found to account for 29.7%, 15.0%, and 16.5% of the total association of GBV with suboptimal adherence, respectively [18]. Adapted from Conroy et al.’s study, [18] Fig. 1 outlines mental health as a mediator of the relationship between GBV and HIV treatment engagement. Young women in Zambia exposed to sexual violence perpetrated by non-partners (i.e., men who are not boyfriends, husbands, or regular partners) have increased odds of depression and anxiety [5]. Improving mental health outcomes may therefore improve HIV treatment and prevention outcomes among these women.

**Fig. 1 Fig1:**
[figure not shown]
Mediating effect of mental health on gender-based violence and HIV

### Hypothesis

We hypothesize that participation in the *Mpata Yathu* intervention may lead to improved HIV-related outcomes (e.g., increased care engagement, adherence, or testing) by reducing depressive symptoms, which are known to interfere with health-seeking behaviors and treatment adherence [39, 40]. Depression has been associated with avoidance, low self-efficacy, and disengagement from care, all of which can negatively impact HIV outcomes [41, 42]. By alleviating these psychological barriers through PST and psychosocial support, participants may improve HIV treatment self-efficacy [39, 43] and therefore become more motivated and emotionally able to engage with HIV prevention or treatment services in the absence of direct HIV-related content. Based on results from a randomized controlled feasibility trial, a PST intervention adapted for pregnant women experiencing depressive symptoms and IPV in rural Ethiopia was feasible, acceptable, and safe to deliver within antenatal care settings [36]. We anticipate that our study will demonstrate similar feasibility, acceptability, and safety when implemented in church-based settings.

Additionally, changing responses to harmful norms may serve as one solution for improving the mental health of young women who have experienced GBV [44]. For example, sexual assault survivors in the Democratic Republic of Congo were perceived as “soiled” or shameful, and these views are associated with worsened mental health outcomes among survivors [45]. Among young women living with HIV and with a history of sexual abuse, HIV-related stigma may also compound the harmful effects of sexual violence on mental health [46]. For our study in Zambia, we anticipate that the problem-solving approach of Friendship Bench will influence how young women think about and respond to normative cultural views of emotions, sexual trauma, and psychopathology [47].

We also anticipate that the PST approach will foster resilience and enhance trauma coping skills surrounding harmful social norms and environmental stressors (e.g., poverty) linked to violence against women [48, 49]. Effective problem-solving skills have been associated with helping women cope with environmental stressors related to abuse [47]. Although PST is effective for treating depression among women who have experienced IPV [47, 50], this study will assess whether PST also improves HIV treatment and prevention outcomes among GBV-exposed women.

## Methods

### Study design

We will conduct a two-arm HT1 randomized controlled trial (RCT) to evaluate the effectiveness and implementation of the adapted Friendship Bench intervention, *Mpata Yathu*, on HIV prevention and treatment, and depression outcomes among young women living with or at risk for HIV, with a lifetime history of GBV and depression symptoms in Zambia. This study will have two arms: an intervention group and a waitlist control group. This trial follows a superiority framework, testing whether the intervention improves outcomes compared with the waitlist control group. The SPIRIT figure [51] (Fig. 2; see Additional file 3 for Checklist) illustrates the timeline of enrollment, intervention, assessments, and close-out procedures for the RCT of the *Mpata Yathu* counseling intervention for AGYW exposed to GBV in Zambia. All items from the WHO Trial Registration Data Set are provided in Additional file 1. The intervention is designed to be delivered in six sessions, with one session per week. However, participants will be given up to 3 months to complete all sessions to accommodate common barriers such as caregiving responsibilities, stigma, mobility, and illness [52–55]. Counseling sessions will be scheduled to accommodate participant availability, and lay counselors will track session completion. After screening and enrollment, eligible participants will be randomized in a 1:1 ratio to either group.*Intervention group:* Participants will receive up to six individual counseling sessions between baseline and 3-month follow-up (0–3 months).*Waitlist control group:* Participants will receive usual care from 0 to 3 months, followed by the intervention (up to six counseling sessions) between 3 and 6 months.

**Fig. 2 Fig2:**
[figure not shown]
SPIRIT figure

Due to the nature of the intervention, participants and lay counselors will not be blinded to study arm assignment. However, quantitative outcome assessors conducting follow-up assessments will be blinded to participants’ group assignment to reduce potential bias in data collection. Unblinding will only occur in cases of adverse events or safety concerns where knowledge of intervention status is necessary for appropriate clinical management or referral.

### Study setting

Our study will be conducted in two churches in Lusaka, one Protestant church in Matero and one Anglican church in Chawama. Our community partners, who are native Zambians, recommended implementation of Friendship Bench within churches in the Matero and Chawama catchment areas of Lusaka since women are disproportionately affected by both poverty and GBV in these areas, aligning with literature linking economic vulnerability to sexual coercion [48]. The selected churches were recommended by native Zambians as appropriate sites for implementation since they serve a wide population and offer the classroom space and organizational structure needed to host counseling sessions.

### Screening and enrollment

We anticipate screening 300 young women over 4 months to enroll 90 eligible participants. We are planning for a conservative dropout rate of 30%. This estimate draws from comparable implementation research in sub-Saharan Africa, including a trial in rural Ethiopia, which used a similar assumption to test feasibility of participant retention and study procedures [56]. This estimate allows us to account for structural barriers (e.g., mobility, stigma, early pregnancy, GBV recurrence, financial hardship, caregiving responsibilities) that commonly affect longitudinal follow-up among AGYW who have experienced GBV [53, 57]. Collecting actual retention data during the RCT will allow us to empirically estimate the true dropout rate and its variability, which will inform the design and sample size calculations of a future fully powered randomized controlled trial and for refining strategies to improve participant retention.

Participants will be considered lost to follow-up for a specific assessment (at 3 or 6 months after the baseline assessment) if they cannot be reached despite at least three documented recontact attempts using various methods (e.g., phone calls, church-based outreach, or home visits, based on participant consent and preference) during the assessment window, defined as ± 1 month from the target follow-up date. Recontact efforts will begin approximately 2 weeks prior to each window and continue throughout. No outreach will occur after the close of each window. Participants who miss the 3-month follow-up assessment may still be contacted and retained for the 6-month follow-up. Participants who voluntarily withdraw from the study will not be considered lost to follow-up.

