### Power analysis

This RCT is powered only to detect intervention effects on symptoms of CMDs, as measured by the SSQ-14, which is the primary outcome. All other quantitative outcomes—including other mental health measures, HIV engagement indicators, and psychosocial variables—will be treated as exploratory and used to inform effect size estimates and future trial design. With the proposed sample size of 126 participants (63 per arm) and using a two-sided alpha level of 0.05, the study will have 80% power to detect a medium effect size of Cohen’s *d* = 0.5 in SSQ-14 scores, which will be analyzed as a continuous outcome. This is a conservative estimate, selected to reflect a clinically meaningful but smaller effect than that observed in the original Friendship Bench trial, which reported a large effect (*d* ≈ 0.75–0.8) over a 6-month period. Accounting for 30% attrition, the sample size estimate was adjusted to account for an original sample size of 180 participants (90 per group). Since our study primarily measures outcomes at 3 months, a smaller effect size is assumed to avoid overestimating power. Between-group comparisons will be conducted at the 3-month follow-up, prior to the waitlist control group receiving the intervention. At 6 months, only within-group analyses will be conducted to assess sustained changes in the intervention group and pre-post change in the waitlist control group. No between-group comparisons will be performed at 6 months.

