### Quantitative data analysis

We will use descriptive statistics to summarize participant characteristics at baseline, feasibility and acceptability metrics, and other implementation outcomes. To assess baseline differences between participants who complete the intervention and those who drop out, we will conduct bivariate comparisons using independent samples t-tests or Wilcoxon rank-sum tests for continuous variables and chi-square or Fisher’s exact tests for categorical variables.

*Primary outcome analysis (powered):* To assess the effect of the adapted intervention on symptoms of CMDs (SSQ-14), we will use mixed-effects linear regression models. This is the only outcome for which the study is statistically powered, based on detecting a standardized mean difference of Cohen’s d = 0.5 at the 3-month follow-up. The model will include:A random intercept for participants to account for within-subject correlation from repeated measures;A fixed effect for time (baseline vs. follow-up);A fixed effect for study group (immediate intervention vs. delayed control);A group × time interaction term to estimate the differential intervention effect over time.

If the model assumptions (e.g., homoscedasticity, normally distributed residuals) are not met, we will consider using generalized linear mixed models with appropriate link functions and distributional assumptions to reduce the risk of Type I and Type II errors.

*Exploratory analyses:* All other outcomes will be analyzed using mixed-effects linear, logistic, or ordinal regression models, depending on the outcome type. These outcomes include:Mental health outcomes: depression (PHQ-9; binary and continuous), anxiety (GAD-7; continuous), and PTSD (CPSS; continuous) symptoms;HIV prevention outcomes (among HIV-negative or status-unknown participants): consistent condom use, PrEP uptake or readiness, HIV risk behaviors (via WAF), and HIV prevention self-efficacy/readiness (via HPRM);HIV treatment outcomes (among HIV-positive participants): ART adherence, clinic attendance, viral load documentation (if available), and HIV treatment self-efficacy (via HIV-SE);

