*Moderation and mediation analyses (exploratory)*: Post hoc exploratory analyses will assess whether changes in mental health outcomes mediate or moderate the intervention’s effects on HIV-related outcomes. Mental health change scores will be calculated separately for each follow-up period (i.e., 3 months and 6 months post-intervention) by subtracting baseline values from the respective follow-up values. This will allow us to assess both short-term and sustained mental health changes and explore their relationship with HIV-related outcomes over time.Mediation: We will test whether changes in CMD symptoms (SSQ-14), depression (PHQ-9), anxiety (GAD-7), or PTSD (CPSS) symptoms help explain (mediate) observed changes in HIV prevention or treatment outcomes using causal mediation models.Moderation: We will include interaction terms between changes in mental health symptoms and intervention group to assess whether the impact of the intervention on HIV outcomes differs depending on mental health changes. Additionally, we will explore whether baseline levels of early adversity (measured by the Adverse Childhood Experiences International Questionnaire; ACE-IQ) [64], social support (measured by the Oslo social support scale; OSSS-3) [66], and coping self-efficacy (measured by the Coping Self-Efficacy scale; CSE) [65] moderate the relationship between the intervention and mental health or HIV outcomes.

*Adjustment variables and stratified analyses:* HIV status (positive vs. negative/unknown) will be included as a covariate in pooled models to adjust for baseline differences. Stratified analyses by HIV status will be considered if each group has a sufficient sample size to support reliable subgroup modeling (e.g., ≥ 40 participants per group). Given the small overall sample size (*N* = 90, accounting for 30% attrition), such stratified analyses may be underpowered and are therefore considered exploratory and hypothesis-generating only. All models will follow an intention-to-treat (ITT) framework, and statistical significance will be assessed at a two-sided *α* = 0.05, with 95% confidence intervals reported. Non-adherence will be handled by analyzing all participants as randomized (ITT); we will also run a pre-specified per-protocol sensitivity analysis defined as completion of ≥ 4/6 sessions and no major protocol deviations. Missing data will be addressed using mixed-effects models, which provide valid estimates under missing-at-random assumptions.

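### The enrolment and analysis sections give a trial total of 90 where the abstract and power section give 90 per arm (180), so the sample size target is not settled

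*Protocol article*

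**What the plan says.** Four places in the protocol article bear on the size of the trial.

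- **Abstract, Methods:** the trial "will be conducted among 90 AGYW, aged 15 to 24, per arm".
- **Power analysis:** "With the proposed sample size of 126 participants (63 per arm"), the design "the study will have 80% power to detect a medium effect size" of d = 0.5, "using a two-sided alpha level of 0.05". After allowance for 30% attrition this becomes an "original sample size of 180 participants (90 per group").
- **Screening and enrollment:** "We anticipate screening 300 young women over 4 months to enroll 90 eligible participants". The next sentence plans for 30% dropout. Nothing there says per arm.
- **Quantitative data analysis, adjustment variables and stratified analyses:** the overall sample size is described as small and given as N = "90, accounting for 30% attrition), such stratified analyses may be underpowered".

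The SSQ-14 at 3 months is the only outcome for which power is claimed; the analysis section bases that claim on "detecting a standardized mean difference of Cohen’s d = 0.5 at the 3-month follow-up".

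**The concern.** Two trial totals, 180 and 90, stand in the current text. The number 90 occurs in the power section only as the enrolled number per arm. It is neither the total enrolled (180), nor the total analysed (126), nor the number analysed per arm (63). In the stratified-analysis text the word overall rules out a per-arm reading, and the mention of attrition does not fit either, since 90 per arm is the figure before losses.

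The enrolment sentence is the only place that ties a screening number and a recruitment period to an enrolment target, so it is the natural source for recruitment planning. If 90 is the real total, the one powered comparison has half its intended sample. If 180 is the real total, the screening projection was written beside the wrong number and may not deliver it.

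**Working it through.** **Inputs, all from the protocol article:** two-sided alpha 0.05, power 80%, d = 0.5, 63 per arm analysed, 90 per arm enrolled (Power analysis); 30% dropout, 300 screened, 90 enrolled, 4 months (Screening and enrollment); 1:1 allocation (Study design).

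**Step 1. Reproduce the plan's own figures.**

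n per arm = 2(1.960 + 0.842)² / 0.5² = 62.8, rounded up to 63, so 126 in total.

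Attrition: 126 / 0.70 = 180, or 63 / 0.70 = 90 per arm.

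Power at 63 per arm (normal approximation): Φ(0.5 × √(63/2) − 1.960) = Φ(0.846) = 80.1%. The t-test gives 79.5%, and 64 per arm would be needed to pass 80%. The power section is correct to rounding.

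**Step 2. The same method with a total of 90.**

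| Reading | Analysed per arm | Power, normal | Power, t-test | Detectable d at 80% power |
|---|---|---|---|---|
| 180 enrolled, 30% lost | 63 | 80.1% | 79.5% | 0.50 |
| 90 enrolled, 30% lost (90 × 0.70 = 63 in total) | 31.5 | 51.0% | 49.7% | 0.72 |
| 90 left after attrition | 45 | 66.0% | 65.0% | 0.60 |

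For the second row: Φ(0.5 × √(31.5/2) − 1.960) = Φ(0.024) = 51.0%. With whole numbers the t-test gives 49.1% at 31 per arm and 50.4% at 32. For the third row: Φ(0.5 × √(45/2) − 1.960) = Φ(0.412) = 66.0%.

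The second row is the direct reading of the enrolment section. The third is possible only if the 90 in the stratified-analysis text means those remaining after losses. They are alternatives, not two ends of one estimate.

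**Step 3. Screening.**

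Yield implied by the enrolment sentence: 90 / 300 = 30%. Yield needed for 180 from 300: 180 / 300 = 60%. Number to screen for 180 at 30%: 180 / 0.30 = 600, or 600 / 4 = 150 a month against 300 / 4 = 75 a month. The article states no yield as such; the 30% exists only if the disputed 90 is right.

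**Step 4. The stratified-analysis rule.** The example threshold is 40 per HIV-status group, so at least 2 × 40 = 80 participants. It cannot be met with 63 analysed. With 90 the smaller group must be at least 40/90 = 44% of the sample; with 126, 40/126 = 32%.

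**The case against.** The strongest reply is that the two places that define the sample agree. The abstract says per arm, and the power section derives 180 by a coherent chain. The simplest account of the other two passages is a dropped per arm or uncorrected text, and then 80% power stands. This is a good argument and limits what can be claimed. A reader might infer that the trial as planned has only 50% to 65% power. The documents do not support that as a fact; it holds only if 90 is the true total.

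Nor do they settle the matter the other way. The error would have to occur in two sections, once with the word overall. The enrolment section and the Conclusion also look ahead to a later, fully powered trial, which fits a smaller real target as well as leftover text.

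Two further inferences are tempting and go too far. One is that recruitment will stop at 90: the sentence is a projection, and nothing makes 90 a cap. The other is that 600 must be screened: if per arm was dropped from the 90 alone, 300 suffices at a 60% yield.

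It can also be said that the planned mixed model uses baseline SSQ-14, so a two-sample calculation understates power. The article gives no baseline to follow-up correlation. Assuming 0.3 to 0.7 with baseline adjustment, so that d becomes d / √(1 − ρ²), power would be about 55% to 79% with 63 analysed and 70% to 91% with 90 analysed. The two-sample figures remain the like-for-like check on the plan's 80%, but they should be presented as that and no more.

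Finally, the stratified analyses are already labelled exploratory, so the effect of the wrong N there is minor.

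**Conclusion.** The contradiction stands and must be corrected. The trial total is 180 in two places and 90 in two others, and 90 matches only the per-arm enrolled figure. Which total governs recruitment cannot be determined from the article.

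The size of the problem depends on the answer. If 180 is right, power is unaffected and the error lies in two sentences and an unreconciled screening projection. If 90 is right, the 80% statement is wrong: by the protocol's own two-sample method, power is about 50% with 90 enrolled and 30% lost, or about 65% with 90 remaining. These figures assume d = 0.5, equal arms, two-sided alpha 0.05 and no gain from baseline adjustment. The case for correction rests on the contradiction in the sample size of the one powered comparison, not on a demonstrated loss of power.

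**What to change.** State one total and use it in the abstract, Screening and enrollment, Power analysis and Quantitative data analysis.

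- **If the total is 180:** change the enrolment sentence to 180 enrolled (90 per arm) and the stratified-analysis text to 180 randomised and 126 analysed. Then reconcile the screening number and the 4-month window: either state and justify the 60% yield that makes 300 enough, or, if 30% is the expected yield, project about 600 screened. The 80% power statement stays.
- **If the total is 90:** correct the abstract and the power section, say whether 90 is before or after attrition, and replace the 80% with about 50% (detectable d about 0.72) or about 65% (detectable d about 0.60) respectively. Any gain claimed from baseline adjustment should come with the assumed correlation.

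By the article's own dates, recruitment was to end in March 2026, before publication in April 2026, so the sponsor should be able to say which target was used. The cost is wording in two sections and a revised screening projection in the first case, and a less favourable stated power in the second.
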